**Methods:**

The clinical study (DRKS00026624) includes two randomized controlled intervention trials with parallel groups, for patients with elective cardiac catheterization and practitioners at the catheterization lab, in two clinic sites of the Ernst-von-Bergmann clinic network in Brandenburg, Germany. Both groups received different interventions for stress management. The intervention for patients comprises a psychoeducational video with different stress management technics and additional a standardized medical information about the cardiac catheterization examination. The control condition includes the in hospitals practiced medical patient education before the examination (usual care). Primary and secondary outcomes are measured by physiological parameters and validated questionnaires, the day before (M1) and after (M2) the cardiac catheterization and at a postal follow-up 6 months later (M3). It is expected that people with standardized information and psychoeducation show reduced complications during cardiac catheterization procedures, better pre- and post-operative wellbeing, regeneration, mood and lower stress levels over time. The intervention for practitioners includes a Mindfulness-based stress reduction program (MBSR) over 8 weeks supervised by an experienced MBSR practitioner directly at the clinic site and an operative guideline. It is expected that practitioners with intervention show improved perceived and chronic stress, occupational health, physical and mental function, higher effort-reward balance, regeneration and quality of life. Primary and secondary outcomes are measured by physiological parameters (heart rate variability, saliva cortisol) and validated questionnaires and will be assessed before (M1) and after (M2) the MBSR intervention and at a postal follow-up 6 months later (M3). Physiological biomarkers in practitioners will be assessed before (M1) and after intervention (M2) on two work days and a two days off. Intervention effects in both groups (practitioners and patients) will be evaluated separately using multivariate variance analysis.

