**Discussion:**

This study evaluates the effectiveness of two stress management intervention programs for patients and practitioners within cardiac catheter laboratory. Study will disclose strains during a cardiac catheterization affecting both patients and practitioners. For practitioners it may contribute to improved working conditions and occupational safety, preservation of earning capacity, avoidance of participation restrictions and loss of performance. In both groups less anxiety, stress and complications before and during the procedures can be expected. The study may add knowledge how to eliminate stressful exposures and to contribute to more (psychological) security, less output losses and exhaustion during work. The evolved stress management guidelines, training manuals and the standardized patient education should be transferred into clinical routines.

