### Experimental Procedure/Intervention

As both patients with an elective cardiac catheterization (CC) examination and practitioners at the catheterization lab face different stressors, both groups received different interventions for stress management.

The CC for the included study participants is elective (non-acute) and medically recommended to evaluate or confirm coronary artery disease, congenital heart disease, heart failure, heart valve disease or aorta dysfunction, heart muscle function and to decide for further treatment. On the admission day (M1), all patients get the usual medical patient information from a cardiologist and anesthetist and get prepared for the examination (fasting, no smoking, evaluation of medication). All patients that fulfill the inclusion criteria concerning age and CC examination will be randomly dedicated to intervention group and control group and subsequently contacted by a research assistant who present the study and its aims and answer all questions. All participants have to sign informed consent after receiving written and verbal information. Afterwards all participants receive the questionnaires for M1 (pre-intervention questionnaire) and only patients in the intervention group get and only patients in the interventions group get the intervention (see The intervention for patients). The next day (M2), all patients get the CC examination at the catheterization lab. During the CC the patient is usually awake and conscious as the hostipal policy is not to administer any tranquilizer, sedatives and anxiolytics as a routine before or during CC procedure. However, patients get sedatives if needed and the type of sedative and dose is documented in a questionnaire by physicians or nurses of the CC lab. After disinfection and local anesthetization of the insertion site (groin, wrist or rarely crook of the arm), the catheter is inserted through a plastic introducer sheath. The catheter is guided through the blood vessel to the coronary arteries and coronary angiography is done by injecting a contrast dye that is visible in X-ray images. The following further diagnostic and interventional procedures can be performed during a cardiac catheterization: myocardial biopsy, levocardiography, right ventriculogram, coronary angiogram, and treatments for narrowing or blockages in the blood vessels like balloon dilatation and stent placement. The aftertreatment includes a bed rest for several hours in the ward until the following day of discharge. The participants fill in the post-intervention questionnaire during the bed rest/stay in the ward (M2).

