
*The intervention for patients* focusses on a video-based standardized patient information about the cardiac catheterization examination and further involves a short patient education with different stress management technics. The video-based standardized patient information gives information about the aim and general process of the CC, like location and aftercare of the puncture, position of the participants during the examination how the procedure is monitored. Further information comprises potential but rare complications and side effects like additional interventions, circulatory disruptions, cardiac arrhythmia, bleedings and (temporary) pain. The second part of the video broaches the issue of stress management technics to handle anxiety, tension and malaise. It provides brief instructions for relaxation, meditation and guided imagery techniques as well as cognitive distraction tasks, and cognitive reframing. All cognitive techniques are easy to apply after one presentation and involve methods to stop negative thoughts, distract from unhelpful thought patterns, to guide attention and positive expectations, to lower tension and support relaxation. For example, the patient should recite the alphabet and imagine a positive thing or event for every letter that he/her would be able to do after the CC. The patient should guide his/her attention to their most pleasant vacation and reactivate the feelings and thoughts present at that time. If a patient feels discomfort or pain, he/she should guide his attention to his/her big toe or left hand for cognitive distraction. The video encourages the patient to speak to the doctors and nurses about complaints and needed assistance. The video is shown to the patients the day before the CC via a tablet bedside in the clinic and is complementary to the non-standardized patient education by the medical doctor that is clinical routine for both intervention and control group.

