### Strategies to Improve Adherence to Interventions

As the intervention video takes only 10 min to watch, adherences strategies for the patients focusses on improved questionnaire return and complete data. To ensure that all questionnaires are completed and returned, a close relationship and support between participant and study staff are stablished. After recruitment, study education and informed consent, participants are asked to fill in the questionnaire for baseline and return it to the staff member. For after-intervention questionnaire (M2) this routine is assured by the nurses at the catheterization ward. To secure the follow-up measurement (M3, 6 months after baseline), a study member contacts the participants via telephone call and sends the questionnaire by post with a prepaid envelope for the return. For the practitioners the adherence strategy focusses on a low-threshold and time-saving training intervention directly at clinic side. Furthermore, adherence problems and barriers are assessed in all follow-up questionnaire. The measurement of HRV on two lab and two leisure days (before and after intervention) is realized by self-applied chest strap heart monitor, a smartphone and an app for the HRV measurement, all provided by the study staff.

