### Outcomes

The primary outcomes for patients are reduced complications and less sedative medication during CC (documented by nurses at the CC lab), and less tension/strain (physiological parameters like pulse, blood pressure, heart frequency), perceived stress (PSS) and better mood (POMS) measured by established and validated self-report questionnaires. Further secondary outcomes for patients are better pre- and post-operative wellbeing, chronic stress (TICS), depression and anxiety (HADS), panic disorder, psychosocial functioning (PHQ-9), life events (ILE), general health (SF-12), satisfaction with health and sleep (41). Additionally, patients are asked about their life style, socioeconomic status and satisfaction about the intervention. At the CC lab, nurses document the behavior of the patients during the cardiac catheterization (agitation, duration of hospital stay, tranquilizer/sedativa use, and level of information) and the number of complications occurred during the procedure. The primary outcomes for practitioners—perceived (PSS) and chronic stress (TICS)—are measured by established and validated self-report questionnaires. Additionally, stress load and recovery are assessed by physiological measurements: circadian profile of HRV (42–44), saliva cortisol (45), alpha-amylase (46) and lysozyme on two working/lab days and two days off as well as the following night, prior to and after the intervention, respectively. The HRV measurements base on beat-to-beat R-R intervals and comprises outcomes for the total activity of the autonomic nervous system [standard deviation of RR intervals (SDNN)], parasympathetic function [root mean sum of squared distance (RMSSD)] and stress load and recovery (number and percentage of R-R intervals lower or >50 msec). Saliva samples are taken on nine defined time points during the day (immediately after awakening, 30, 45, 90, 150 min after awakening, before lunch, 4 p.m., before dinner and going to bed) on a working/lab day and day off. Weight and mood (POMS) are assessed simultaneously as control variables. The practitioners are further asked about vital exhaustion (VE), anxiety and depression (HADS), tension, effort-reward imbalances (ERI), social support (BSSS), satisfaction with health and sleep (41) as well as life style, socioeconomic status, expectations and adherence (barriers) to the intervention program.

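### Better pre-operative wellbeing is a stated patient outcome, but no patient self-report is taken between the video and the catheterization, so that part of the outcome cannot show a video effect

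*Protocol article*

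**What the plan says.** The Outcomes section lists, for patients: "Further secondary outcomes for patients are better pre- and post-operative wellbeing, chronic stress (TICS), depression and anxiety (HADS". The Methods part of the abstract gives the same aim as an expected result of the video: "better pre- and post-operative wellbeing, regeneration, mood and lower stress levels over time". The Discussion part of the abstract adds an expectation for patients and practitioners together: "In both groups less anxiety, stress and complications before and during the procedures can be expected".

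The timing is set out under Experimental Procedure/Intervention and in Strategies to Improve Adherence to Interventions:

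- On the admission day, after consent: "Afterwards all participants receive the questionnaires for M1 (pre-intervention questionnaire". This form is handed back as the baseline: "participants are asked to fill in the questionnaire for baseline and return it to the staff member".
- The intervention arm then gets the video: "The video is shown to the patients the day before the CC via a tablet bedside in the clinic".
- The procedure follows: "The next day (M2), all patients get the CC examination at the catheterization lab".
- The next self-report comes after it: "The participants fill in the post-intervention questionnaire during the bed rest/stay in the ward (M2".

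Table 1 has columns for M1, M2 and M3 only. The sole extra entries, marked with an asterisk, are behavior and physiological parameters during the catheterization.

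**The concern.** The outcome is worded as an improvement in wellbeing before the procedure. To show that, the patient's state has to be recorded after the video has been seen and before the catheterization starts. The schedule takes one self-report before the video and the next after the procedure, and none in between.

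What is at stake is what the trial may conclude. As written, the report could present balance at M1 as a failure to improve pre-operative wellbeing, or present an M2 result as a pre-operative benefit. Neither would be correct. The gap is not a detail left to a fuller document, because the article itself fixes the order of events and the measurement table.

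**Working it through.** The plan gives no figure for this outcome, so there is none to reproduce. The check is to put the events in order and look for a self-report in the relevant window.

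1. **Order of events for a patient in the intervention arm** (Experimental Procedure/Intervention; Strategies to Improve Adherence to Interventions): consent, M1 questionnaire, video, catheterization the next day, M2 questionnaire during the ward stay, M3 by post six months after baseline. The control arm has the same order without the video.

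2. **Instruments by time point** (Table 1):
   - HADS and POMS: M1 and M2.
   - Visual analog scales for pain and for satisfaction with health and sleep: M1, M2 and M3.
   - PSS-10, TICS, PHQ-9 and SF-12: M1 and M3.
   - No row is labelled wellbeing. Whichever of these instruments is meant to represent it, the timing problem is the same.

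3. **Count.** Self-report time points before the catheterization: 1 (M1). Of these, after the video: 0. First self-report after the video: M2, which is also after the catheterization.

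4. **The M2 label does not change the count.** Study Design equates M2 with the examination day, and Table 1 places it on the day after. On both, the M2 questionnaire follows the procedure.

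5. **Consequence for an arm comparison of the pre-operative value.** Let μ be the mean of any self-report at M1. Since M1 precedes the video, the video cannot alter it, so under randomisation

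   expected difference = μ(video arm) − μ(control arm) = μ − μ = 0,

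   whatever the video's true effect. At the two-sided 0.05 level in Statistical Analysis, the chance of a significant result is 0.05, with 60 per group or any other number.

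6. **A caveat on the zero.** Under Experimental Procedure/Intervention, patients are allocated first and approached for consent afterwards. If consent differed by arm, M1 could differ too. That difference would come from selection and still not from the video.

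**The case against.** The strongest reply is that the phrase may only describe a pre-post design: M1 is the value before the procedure, M2 the value after it, and no test of M1 between arms is planned. It is true that the article proposes no such test. But the wording lists *better* pre-operative wellbeing as an outcome, and the abstract expects it as a result of the intervention. A baseline cannot fill that role.

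A reader might also infer three stronger points that the documents do not support.

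- *That pre-operative anxiety is likewise a defined outcome.* In the Outcomes sentence the words for before and after the operation qualify wellbeing. HADS is listed without a time, and its use at M1 and M2 is a coherent pre-post measure. Less anxiety before the procedure is only an expectation in the abstract's Discussion.
- *That nothing informative is recorded around the procedure beyond pulse, blood pressure and heart frequency.* Outcomes also has nurses document agitation, sedative use and complications, and the article states that laboratory practitioners are blinded to patient allocation. These observations can reflect the video. They still do not measure how the patient felt beforehand.
- *That M2 is so diluted by relief that a working video would look ineffective.* Relief common to both arms cancels in the randomised contrast. Loss of power would require relief to shrink the arm difference, and the article gives no figure for that. The Introduction also treats postoperative pain and wellbeing as affected by anxiety, so M2 is a target in its own right.

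These limits narrow the point but do not remove it.

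**Conclusion.** The point holds for the pre-operative part of the wellbeing outcome and for the abstract's expectation of less anxiety and stress before the procedure, so far as these rest on self-report. With no self-report between video and catheterization, the expected arm difference in the only pre-operative value is zero and the data cannot show a video effect there.

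This rests on M1 being completed before the video, as the article states, and on randomisation without arm-dependent consent for the exact zero. It needs no assumed effect size.

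The damage is confined. A secondary outcome is affected; the primary outcomes recorded during the procedure are not, and wellbeing, mood and HADS at M2 remain testable. The change is worth making because it is cheap and decides whether the trial can make a claim that it announces.

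**What to change.** Add one or two short visual analog items, for tension and for wellbeing or anxiety, in both arms on the ward after the video and before the procedure. A tension scale of this type is already used for practitioners (Table 2). Add the time point to Table 1, and define pre-operative wellbeing as this value compared between arms with adjustment for M1.

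The cost is a protocol amendment, one more short form for the ward nurses who already see to M2, and some missing values. Asking about tension shortly before the procedure may also draw attention to it, though equally in both arms. Study Status says that first participants have already been assessed; they cannot supply the new value, so the outcome would cover only patients enrolled after the change, and the report should say so.

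If the items cannot be added, remove the pre-operative part from the wellbeing outcome, limit self-report claims to the state after the procedure, and bring the two abstract statements into line. That costs only a change of wording.

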### Randomization Procedure and Blinding

The process of randomization to the allocation arm was performed prior to recruitment via a randomization list. This randomization list was generated via the computerized randomization tool Research Randomizer (https://www.randomizer.org/). Participants will be randomly assigned to either the intervention or control condition according to the randomization list. Patients and practitioners cannot be blinded due to their active role in the intervention. Practitioners at the cardiac catheterization laboratory are blinded to the group allocation of the patients.

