Details on outcomes, questionnaires and measurement points are provided in Table 1 for participants and Table 2 for practitioners.

**Table 1 T1:** Outcome measurements for patients with elective cardiac catheterization.

**Outcome**	**Measurement**	**Assessment**		
		**M1** **(day before CC)**	**M2** **(day after CC)**	**M3** **(6 months after M1)**
Chronic stress	Trier inventory for chronic stress (TICS) (47)	X		X
Perceived stress	Perceived stress scale-−10 items (PSS-10) (48, 49)	X		X
Life events	Inventory of stressful life-events (ILE) (50)		X	
Depression	Patient health questionnaire-−9 items (PHQ-9) (51)	X		X
Anxiety and depression	Hospital anxiety and depression scale (HADS) (52, 53)	X	X	
Health-related quality of life	Short form health-−12 items (SF-12) (54)	X		X
Pain	Visual analog scale (VAS)	X	X	X
Mood	Profile of mood state (POMS) (55, 56)	X	X	
Satisfaction with health and sleep	Visual analog scale (VAS)	X	X	X
Life style factors	Physical activity, smoking, alcohol consumption, medication, critical life events	X		X
Sociodemographic characteristics	Sex, Age, education, marital status, job position, income	X		
Satisfaction with intervention			X	
Behavior while CC*				
Physiological parameter while CC*	Pulse, blood pressure, heart frequency	X	X	

**(additional) measurement during CC*.

**Table 2 T2:** Outcome measurements for practitioners at the catheterization lab.

**Outcome**	**Measurement**	**Assessment**		
		**M1** **(before intervention)**	**M2** **(after intervention)**	**M3** **(6 months after M1)**
Chronic stress	Trier inventory for chronic stress (TICS) (47)	X		X
Perceived stress	Perceived stress scale-−10 items (PSS-10) (48, 49)	X		X
Effort-reward imbalances	Effort-reward imbalances questionnaire (ERI) (57)	X		X
Anxiety and depression	Hospital anxiety and depression scale (HADS) (52, 53)	X	X	
Vital exhaustion	Maastricht vital exhaustion questionnaire (VE) (58)	X	X	
Tension	Visual analog scale (VAS)	X	X	X
Mood	Profile of mood state (POMS) (55, 56)	X	X	
Satisfaction with health and sleep	Visual analog scale (41)	X	X	X
Life style factors	Physical activity, smoking, alcohol consumption, medication, critical life events	X		X
Social support	Berlin social support scale (BSSS) (59)		X	
Sociodemographic characteristics	Sex, age, education, marital status, job position, income	X		
Expectation of/satisfaction with intervention		X	X	
Heart rate variability	Activity of the autonomic nervous system (SDNN), parasympathetic function (RMSSD)	X	X	

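### Life events (ILE) are listed as a secondary outcome of the patient video but asked only at M2, one to two days after it, so an arm difference could not be read as an effect on life events (low priority)

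*Protocol article*

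**What the plan says.** In the protocol article, the Outcomes section opens its list of secondary endpoints for patients with "Further secondary outcomes for patients are better pre- and post-operative wellbeing" and continues through a run of instruments that includes "psychosocial functioning (PHQ-9), life events (ILE), general health (SF-12". Life style, socioeconomic status and satisfaction with the intervention follow in a separate sentence, as things patients are asked in addition. By its position, the ILE is classed with the outcomes and not with the background items.

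Table 1 gives the schedule. The row "Inventory of stressful life-events (ILE) (50" has a mark at M2 only. A different row, life style factors, covers "Physical activity, smoking, alcohol consumption, medication, critical life events" and is marked at M1 and M3.

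On timing, the section Experimental Procedure/Intervention places the video after the M1 questionnaire: "The video is shown to the patients the day before the CC via a tablet bedside in the clinic". It places the later questionnaire after the procedure: "The participants fill in the post-intervention questionnaire during the bed rest/stay in the ward (M2". The adherence section gives the length of the video: "As the intervention video takes only 10 min to watch". On blinding, the article states: "Patients and practitioners cannot be blinded due to their active role in the intervention".

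**The concern.** A variable listed as an outcome will be compared between arms, and a difference will be read as an effect of the intervention. For that reading to be possible, the quantity measured must be able to change between the intervention and the assessment. An inventory of past stressful events completed a day or two after a short video hardly meets that condition, because nearly everything it asks about had already happened.

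The comparison would then be uninterpretable. A null result says nothing about the video. A positive result would be chance or a difference in how patients report events. The second is conceivable, since patients know what they received and the video teaches reframing and stopping of negative thoughts.

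A smaller point follows from the same schedule. Stressful events are naturally used as background information on stress exposure, and for that use a value taken before the video is preferable to one taken after it.

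**Working it through.** No stated figure has to be reproduced. The point rests on the role given to the ILE and on when it is asked.

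**Sequence for a patient**

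1. Admission day: M1 questionnaire without the ILE, then the video in the intervention arm.
2. Next day: catheterization in both arms.
3. During the ward stay after the procedure: M2 questionnaire with the ILE. The Study Design section equates M2 with the examination day and Table 1 labels it the day after, so the gap from video to ILE is about 1 to 2 days.
4. Six months after M1: M3 questionnaire without the ILE.

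**Coverage in Table 1.** I count ten self-report rows that could be repeated: TICS, PSS-10, ILE, PHQ-9, HADS, SF-12, pain, mood, satisfaction with health and sleep, and life style factors. Nine of the ten are marked at M1, five at M2 and seven at M3. The ILE is the only one without an M1 mark, so it yields neither a change score nor a pre-video value.

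**Share of the recalled period that the video could influence.** The recall window is not in the documents, so I assume a range.

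Share after the video = days from video to M2 / length of window in days

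| Assumed window | 1 day after video | 2 days after video | Share before the video |
|---|---|---|---|
| 1 month (30 days) | 1/30 = 3.3% | 2/30 = 6.7% | 93.3% to 96.7% |
| 3 months (91 days) | 1/91 = 1.1% | 2/91 = 2.2% | 97.8% to 98.9% |
| 6 months (182 days) | 1/182 = 0.55% | 2/182 = 1.1% | 98.9% to 99.45% |
| 12 months (365 days) | 1/365 = 0.27% | 2/365 = 0.55% | 99.45% to 99.73% |

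Even with the shortest window and the longest gap, about 93% of the period precedes the video. The remaining one or two days are spent in hospital around the procedure.

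**What could still separate the arms.** Both arms undergo catheterization, so the procedure by itself does not create a difference. That leaves chance and arm-dependent recall or rating. The documents give no evidence that such reporting differences occur. They are possible because patients are not blinded.

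**The case against.** The strongest reply is that this is loose wording and not a planned efficacy claim. The word for improvement in the secondary-outcome sentence sits next to wellbeing, and the hypotheses in the Abstract, Introduction and Discussion never predict fewer life events. That is fair. A reader might infer that the trial expects the video to reduce life events, but the article does not say so. What stands is that the ILE appears in the outcome sentence, apart from the background items, and that the published schedule matches neither an outcome nor a baseline variable.

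Four other tempting readings also go too far.

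- **That no pre-video information on life events exists.** Table 1 asks about critical life events at M1 and M3 under life style factors. This is a different item from the ILE and may be rougher, but it exists.
- **That the M2 timing spoils a planned adjustment.** The Statistical Analysis section names sociodemographic data, sedative medication and adherence as control variables. The ILE is not among them.
- **That the plan contains an ILE test with a 5% chance of a false effect.** The section describes a multivariate variance analysis and a two-sided 0.05 level, with no separate ILE test.
- **That the true effect is exactly zero.** Whether the inventory counts events or rates their burden is not stated. If it rates burden, a video on reframing might shift the score. That would be an effect on appraisal, not on the occurrence of events.

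It can also be said that M1 already carries most of the questionnaires on a busy admission day, so M2 may have been chosen to spread the load. The article gives no reason, but the burden is real and counts as a cost of the change.

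**Conclusion.** The point holds as a low-priority one. As published, the ILE is a secondary outcome measured once, about one to two days after a 10-minute video, and such a measurement cannot show an effect on life events. For assumed recall windows of 1 to 12 months, about 93% to more than 99% of the recalled period precedes the video. The conclusion depends on the window being of roughly that order or longer, and on the inventory asking about past events, as its name indicates.

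The consequences are small: one secondary measure is affected, and neither the primary outcomes nor the sample size is touched. This is not something that can be left wholly to an analysis plan. Such a plan could relabel the variable, but it could not recover an ILE value from before the video.

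**What to change.** 1. Remove the ILE from the list of secondary outcomes and describe it as a background variable. This costs nothing and can be done for all patients, including those already assessed.
2. For patients not yet enrolled, move the form from M2 to M1, to be completed before the video. No items or visits are added and M2 becomes shorter. M1 becomes longer, on a form that already carries nine of the ten self-report rows. Allocation comes before M1 in this trial, so the gain is a pre-video value, not a pre-allocation one.
3. Record for each patient whether the ILE was completed at M1 or M2. The Study Status section says that first participants have been recruited and assessed, so timing will be mixed and any use of the variable should take account of that.
4. If life events are to remain an outcome, assess the ILE at M3 with the reference period restricted to the interval since M1, so that the events counted fall after the intervention. This adds one form to the postal follow-up, and the answers remain unblinded self-report.
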